#### Collected variables

The following clinical variables will be collected per volunteer:

Age (years).Mammographic breast density, rated according to the radiologist’ BI-RADS assessment: A (breasts of fat density), B (breasts with areas of scattered fibroglandular tissue), C (heterogeneously dense breasts), D (extremely dense breasts).Breast (right/left) and quadrant (superior/inferior/lateral/medial) where the lesion is located (if present).BI-RADS score of the screening mammographic study for each breast (2D or tomosynthesis) according to the degree of suspicion (nominal qualitative variable).Breast type assigned by MammoWave (nominal qualitative variable): WSF, NSF.Radiological findings in the mammographic readings made by radiologists (none, nodule, microcalcifications, distortion or asymmetric density).Additional tests (US, MRI) performed, with correspondent outcomes (BI-RADS score, confirmed presence of BC, not conclusive, confirmed absence of BC).Biopsy performed, if any, with outcomes. When a biopsy is performed, the kind of method (fine-needle aspiration biopsy or core needle biopsy), histology of the lesion and immunohistochemistry are recorded as:Histopathological evaluation of BC according to typology (infiltrating ductal carcinoma, infiltrating lobular carcinoma, ductal carcinoma in situ and other types).Histopathological evaluation of BC according to tumour grade (I, II, III).Molecular evaluation of BC (luminal A, luminal B, HER-2 positive, triple negative).Size of the confirmed lesion of BC (tumour), according to the tumour, node and metastases (TNM) staging system^39^ (T0: no evidence of primary tumour; T1mi: tumour less than or equal to 1 mm; T1a: tumour between 1 and 5 mm (included); T1b: tumour between 5 mm and 1 cm (included); T1c: tumour between 1 and 2 cm (included); T2: tumour between 2 and 5 cm (included); T3: tumour larger than 5 cm; T4: tumour of any size with involvement in skin, chest wall or inflammatory BC).Lymph node involvement of BC, according to TNM staging system (N0: no evidence of BC in lymph nodes or areas of BC less than 0.2 mm; N1: spread of BC in 1–3 internal axillary or mammary nodes; N2: spread of BC in 4–9 axillary nodes/spread of BC in internal mammary nodes, but not in axillary; N3: spread of BC to 10 or more nodes/spread of BC to supraclavicular or infraclavicular nodes).BC stage according to TNM staging system (0, IA, IIA, IIB, IIIB, IIIC).Suggested surgical treatment (conservative (quadrantectomy/lumpectomy); radical).Women’s satisfaction (a properly designed questionnaire collecting women’s issues and plus during the exam with MammoWave in the language spoken by the women).Adverse events (AEs).

#### Study outcomes

The primary outcomes will be measured as follows:

MammoWave’s sensitivity (percentage of ‘true positive’ results) while using an optimised AI-based classification algorithm.MammoWave specificity (percentage of ‘true negative’ results) while using an optimised AI-based classification algorithm.

The secondary outcomes will be measured as follows:

BC detection rates of each system by type of lesion (microcalcification, mass, asymmetry or architectural distortion group).BC detection rates, recall and positive predictive value (biopsy) of each system, also by breast density (types A and B being low-density breasts (fat), C and D high-density breasts (high content of fibroglandular tissue)).BC detection rates of each system by BI-RADS classification.^37^BC detection rates of each system by type of lesion (microcalcification, mass, asymmetry or architectural distortion group) and density (fat or high content of fibroglandular tissue).Programme screening rate, calculated as the proportion of women diagnosed with BC in the study population.BC detection rates of each system by histological type and size of the BC and BI-RADS classification.^37^MammoWave’s AI classification algorithm’s sensitivity (frequency of ‘true positive’ results) and specificity (frequency of ‘true negative’ results) after a retrospective adjustment using the data at the end of the study.BC detection rate, recalls and positive predictive value (biopsy), also by breast density (types A and B or C and D) after retrospective AI adjustment using the data at the end of the study.Programme screening rate, calculated as the proportion of women diagnosed with BC in the study population after a retrospective adjustment using the data at the end of the study.Evaluation of the reproducibility of results comparing the lectures performed at the study centres and the centralised lectures.Volunteers’ satisfaction through a properly designed questionnaire collecting women’s issues during the exam with MammoWave in the language spoken by the women.

Regarding safety outcomes, all the events will be registered, and they will be identified as related or not to MammoWave.

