Evaluation of the sensitivity of MammoWave in detecting BC according to the American College of Radiology (ACR) BI-RADS classification.^37^Evaluation of the effectiveness of MammoWave versus a conventional reading of digital mammographic images (either 2D or tomosynthesis) and analysis of whether they are equivalent in terms of detection rates of BC (sensitivity),the number of recalls and positive predictive value (for the biopsies performed).Evaluation of the detection rate (sensitivity) of each system according to the type of mammographic radiological finding (microcalcification, mass, asymmetry or architectural distortion group).Evaluation of the impact of breast density (according to the ACR BI-RADS classification^37^ assigned by the radiologist, with or without automatic software if available) on the MammoWave detection rate of BC, number of recalls and positive predictive value (of the biopsies performed).Evaluation of the impact of breast density (according to BI-RADS classification assigned by the radiologist^37^) on the detection rate (sensitivity) of each system depending on the type of finding (microcalcification, mass, asymmetry or architectural distortion group).Comparison of radiological, histological and stage characteristics between the BCs detected by each system.Evaluation of the reproducibility of the AI-based MammoWave software’s results.Evaluation of the improvement in both sensitivity and specificity when retrospectively using AI algorithms to evaluate MammoWave data after its further optimisation with all the data collected in the patients included in the study.Volunteers’ satisfaction related to MammoWave use, through a properly designed questionnaire (given here as online supplemental material), collecting women’s issues during the exam with MammoWave in the language spoken by the women.

Additionally, there is a secondary objective, which is related to MammoWave safety and tolerability assessment. Furthermore, an additional exploratory objective of the clinical study is to establish a predictive model capable of discriminating and classifying lesions in MammoWave outcomes for volunteers with breast lesions, if feasible.

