**Figure 3 F3:**
[figure not shown]
Study design and recruitment process. AI, artificial intelligence; BC, breast cancer; DBT, digital breast tomosynthesis; DM, digital mammography.

Women attending the centres for their scheduled mammogram appointment (or those who have had a mammogram within the past month) will receive information about the study and will be invited to participate on a voluntary base. Women who agree to participate, meet the inclusion and exclusion criteria and sign their informed consent document will undergo the MammoWave examination. All the eligible women will be enrolled consecutively. The reason for non-participating in the study (fear of the new exam, lack of time, lack of information, lost-to-follow-up, breasts size larger than MammoWave’s cup) will be recorded by the investigators.

On completion of MammoWave’s scan of each breast, the data will undergo processing in a cloud platform to enable real-time and high-speed data processing. The output from MammoWave will primarily consist of microwave images (along with parameters that characterise these images) and will include the label generated by the novel AI-based classification algorithm; the label will be then used for final analysis by comparing it with conventional imaging results. Thus, the microwave images (which lack detailed morphological definition) and their associated features will not serve as a basis for diagnostic decisions made by radiologists or investigators.

Regarding intervention, if MammoWave’s results (ie, labels provided by its AI classification system) indicate WSF and there is a disagreement between MammoWave output and conventional mammographic imaging, additional examinations may be warranted. These may include US, if not already conducted, particularly for dense breasts, aligning with EUSOBI recommendations due to the reduced sensitivity of conventional mammography in dense breasts.^38^ All output information, including MammoWave’s results and conventional breast examination findings, will be collected and incorporated into this study. At each site, the investigators will prospectively compare MammoWave labels with the reference standard. Furthermore, on the study’s conclusion, the MammoWave labels will undergo centralised review by blinded specialists who will not have access to the reference standard. This review aims to validate the AI-produced data.

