### Analysis

#### Number of participants

The maximum number of participants will be 10 000 (for all the sites). The sample size was determined using the Buderer approach,^40^ considering that (1) the primary objective of the study is to confirm that MammoWave reaches sensitivity >75% and specificity >90% in BC detection on 10 000 volunteers undergoing breast screening, (2) a two-tailed 95% CI for sensitivity and specificity (CI width=10) and (3) a prevalence of female BC detected due to screening of 0.92%, according to the official English statistics of the National Health Service (NHS) Breast Screening Programme.^41^ A minimum of 8000 participants is required to reach the primary endpoint.

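### Recall and biopsy PPV are to be compared between systems, but no biopsy follows from a positive MammoWave label alone, so its biopsy PPV is not comparable with mammography's

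*Protocol article*

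**What the plan says.** The secondary objectives (Hypothesis and objectives) ask whether MammoWave and conventional mammographic reading are equivalent in detection, "the number of recalls and positive predictive value (for the biopsies performed"). The Study outcomes section repeats this as "BC detection rates, recall and positive predictive value (biopsy) of each system, also by breast density".

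The Study design section sets out what follows a label:

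- **Phase 1 (500 women):** everyone has mammography and ultrasound, whatever the label.
- **Phase 2 (9500 women):** a positive label is followed by an ultrasound unless one was already done. This is worded as something that will happen.
- **Later in the same section (after Figure 3):** if the label is WSF and "there is a disagreement between MammoWave output and conventional mammographic imaging, additional examinations may be warranted". This is worded as optional, with ultrasound as one possibility.
- **Biopsy:** suspected cases follow each site's standard pathway, which may include MRI and biopsy. No biopsy rule refers to the label.

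Two further outcomes apply to the algorithm re-tuned at the end of the study: "BC detection rate, recalls and positive predictive value (biopsy), also by breast density (types A and B or C and D) after retrospective AI adjustment" and "Programme screening rate, calculated as the proportion of women diagnosed with BC in the study population after a retrospective adjustment".

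The Follow-up section names two years of follow-up of each volunteer as the reference standard for comparing detection, recalls and PPV. The article does not say what counts as a MammoWave recall, or how a biopsy is attributed to one system.

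**The concern.** A PPV restricted to biopsies performed describes a test only through the women who reach biopsy. A WSF woman reaches biopsy only if another modality also raises suspicion. WSF women cleared by mammography and ultrasound, who would be most of the label's false positives, never enter the denominator. Mammography's biopsies also pass through work-up, but there the test's own suspicion starts the pathway. The two figures are selected differently, and the equivalence question rests on them.

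Among biopsies led by mammography alone, a label carrying no information would reproduce the yield of the biopsies it is drawn from. Apparent equivalence on this measure would then say nothing about the device.

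The retrospective outcomes raise a related problem. A woman who becomes WSF only on re-scoring had no work-up prompted by that label. The programme screening rate, defined as the proportion of women diagnosed, contains no term that the label could alter.

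**Working it through.** **Inputs from the article (Number of participants).** The targets are that "MammoWave reaches sensitivity >75% and specificity >90% in BC detection on 10 000 volunteers undergoing breast screening". The section also gives "a prevalence of female BC detected due to screening of 0.92" per cent, and "a two-tailed 95% CI for sensitivity and specificity (CI width=10").

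**The plan's own figure.** Buderer's formula is n = z² × Se(1 − Se) / (W² × prevalence). With Se 0.75, W 0.10 and prevalence 0.0092:

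n = 1.96² × 0.75 × 0.25 / (0.10² × 0.0092) ≈ 7830

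This is 2.1% below the stated minimum of 8000. The match requires the 10 points to be the half-width. It confirms that 75% and 0.92% are the working values. The article gives no figure for recall or biopsy PPV.

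**PPV over all WSF women** (10 000 women, targets applied per woman):

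- Cancers: 10 000 × 0.0092 = 92; WSF with cancer: 0.75 × 92 = 69
- WSF without cancer: 0.10 × 9908 = 990.8
- WSF in total: 1059.8, a rate of 10.6%
- PPV = 69 / 1059.8 = 6.5%

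Per breast, with prevalence halved, PPV is about 3.3%.

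**Biopsy PPV among WSF women.** None of the next three inputs is in the article; all are assumed:

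- b, the cancer yield of mammography-led biopsies: 20% to 40%
- f, the share of benign biopsied women labelled WSF: 10% (label independent of biopsy selection given disease status) or 30%
- u, the share of the remaining false-positive WSF women biopsied after a label-triggered ultrasound: 0 to 10%

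All 92 cancers are taken to be among the mammography-led biopsies, and the extra biopsies find no further cancers. Benign mammography-led biopsies number B = 92(1 − b)/b, which is 368 at b = 20% and 138 at b = 40%. Then

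PPV = 69 / [69 + fB + u(990.8 − fB)]

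| b (mammography-led yield) | f | u = 0 | u = 10% |
|---|---|---|---|
| 20% | 10% | 69/(69 + 36.8) = 65.2% | 69/(69 + 36.8 + 95.4) = 34.3% |
| 40% | 10% | 69/(69 + 13.8) = 83.3% | 69/(69 + 13.8 + 97.7) = 38.2% |
| 20% | 30% | 69/(69 + 110.4) = 38.5% | 69/(69 + 110.4 + 88.0) = 25.8% |
| 40% | 30% | 69/(69 + 41.4) = 62.5% | 69/(69 + 41.4 + 94.9) = 33.6% |

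The range is roughly 34% to 83%, apart from one corner at 26%. At b = 20% every entry is above mammography's 20%. At b = 40% both entries with u = 10% fall below 40%. The order reverses once u passes (172.5 − 69 − 13.8)/977 = 9.2% for f = 10%, or (172.5 − 69 − 41.4)/949.4 = 6.5% for f = 30%, where 172.5 = 69/0.40.

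**Uninformative label.** If cancers and benign cases are labelled WSF equally often, PPV among mammography-led biopsies equals b: 20% at b = 20% and 30% at b = 30%.

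**Retrospective programme rate.** The numerator is women diagnosed and the denominator is the study population. Re-scoring stored signals changes neither, so over the same women and follow-up the adjusted and unadjusted rates are identical.

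**The case against.** Several stronger readings are tempting, and the article does not support them.

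- **That the label has no effect on recall or biopsy.** In phase 2 a positive label leads to ultrasound, and suspected cases can go on to biopsy. The text after Figure 3 leaves other examinations open. What stands is narrower: no biopsy follows from the label alone, and a MammoWave recall is not defined in the article.
- **That MammoWave must look better than mammography.** The direction depends on biopsy yield and on how many label-prompted ultrasounds end in biopsy. The article gives neither, and the table contains cases in both directions.
- **That mammography's figure is unfiltered.** Its biopsies also follow work-up. Any biopsy PPV is expected to exceed the PPV of the initial test, so the gap from 6.5% is partly definitional. The fault is the unequal selection between systems.
- **That the false positives are hidden.** Specificity is a co-primary outcome on the full analysis set, so unbiopsied false positives count there. The 2-year reference standard also allows a PPV over all WSF women.
- **That nothing can be computed after re-scoring.** A WSF rate and a label PPV can be. A biopsy PPV among re-scored positives can be too, and may differ from the original, but it remains conditional on the original work-up.

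Attribution rules may be in the full protocol or the SAP, and their absence from the article is not held against it. They would not settle the matter: the article fixes the denominator as biopsies performed, and no attribution rule brings unbiopsied women into it.

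**Conclusion.** The concern holds as a defect in secondary outcomes that carry the comparison with mammography; the primary analysis is untouched. Biopsy PPV for each system is not a like-for-like comparison, because a WSF woman needs suspicion on another test to be biopsied while mammographic suspicion opens the pathway itself. At the protocol's targets the gap between the two possible MammoWave figures is large: 6.5% over all WSF women against roughly 34% to 83% among those biopsied. The first figure rests only on the protocol's own values applied per woman. The second rests on the assumed yields, labelling rates and biopsy rates shown. No claim that MammoWave will be favoured over mammography follows from the documents. The fault in the retrospective programme screening rate needs no assumption.

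**What to change.** - **For the comparison between systems,** define a MammoWave positive as WSF in either breast. Report the WSF rate and cancers divided by all WSF women, against the 2-year reference standard. Set these beside mammography's recall rate and PPV of recall in the same women.
- **For biopsy PPV,** report the combined trial pathway, split by which test prompted the biopsy.
- **For the retrospective algorithm,** report WSF rate and label PPV as virtual measures, label any biopsy PPV as conditional on the original work-up, and delete the programme screening rate.
- **Reconcile the two Study design statements** of what follows a WSF label. One makes ultrasound a set step and the other makes further examination optional.

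The cost is outcome wording in the protocol and SAP. Labels, BI-RADS scores, additional tests, biopsies and follow-up are already to be collected. With last recruitment planned for February 2026, two years of follow-up end about February 2028, so figures at the December 2026 evaluation would be provisional. The downside for the sponsor is that MammoWave's reported PPV becomes less favourable.

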#### Study design

This is an open, multicentric, interventional, prospective, non-randomised clinical investigation in which 10 000 volunteers undergoing conventional breast screening examination will also undergo the MammoWave exam. Recruitment of volunteers will be performed at nine centres in different European countries: two Italian hospitals (IRCCS Policlinico San Martino, Genova; and Ospedale San Giovanni Battista—USL Umbria 2, Foligno), one Polish hospital (Pomeranian Medical University Hospital, Szczecin), two Portuguese centres (Champalimaud Foundation, Lisbon and Clínica [name] Ângelo, Lisbon), three Spanish hospitals (Hospital Universitario de Toledo, Toledo; Hospital Universitario Reina Sofía, Córdoba and Hospital General Universitario Morales Meseguer, Murcia) and one Swiss hospital (University Hospital, Zurich). The study (see figure 3) will be composed of two phases:

A preliminary phase is planned to validate and fine-tune the optimised MammoWave’s AI classification algorithm. During this phase, the initial cohort will consist of 500 women recruited from all participating clinical sites. In this preliminary stage, all asymptomatic volunteers will undergo conventional mammography and ultrasound (US) examinations at a minimum to ensure optimal diagnostic accuracy. Suspected cases will follow the standard site-specific pathways, which may include additional tests such as MRI and biopsy.During the second phase, the remaining 9500 women will be enrolled. If the MammoWave’s AI label is positive, an US examination will be conducted (in addition to conventional mammography), particularly for women with dense breasts (recall, as per the European Society of Breast Imaging (EUSOBI), recommendations for screening in dense breasts^38^), unless such examination has already been performed. Suspected cases will follow the standard site-specific pathways, which may include additional tests such as MRI and biopsy. After the enrolment of 3000 volunteers, an interim evaluation will be carried out.

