#### Choice of comparator/control intervention

MammoWave’s results (labels provided by its AI-based classification algorithm) will undergo validation against a reference standard, which represents the output of the conventional breast examination pathway. This pathway includes screening mammograms conducted with DM or DBT, integrated with other radiological/histological findings as required by the responsible investigator, following the site’s ongoing procedures and clinical circuit. The reference standard’s results will be categorised as ‘positive’ when BC presence is confirmed by histology (ie, BI-RADS 6), otherwise labelled as ‘negative’ (BI-RADS 1, 2 or 3). Specifically, within this study BI-RADS 4 and BI-RADS 5 are only image suspicion criteria: when a biopsy is performed, they will be categorised as ‘positive’ when BC presence is confirmed by histology (ie, BI-RADS 6), otherwise labelled as ‘negative’ (BI-RADS 1, 2 or 3).

Conventional mammogram studies (2D or tomosynthesis) will adhere to approved protocols and clinical practices for breast screening. Radiological reports and interpretations will align with international guidelines, particularly those set by the ACR.^37^ The radiologists involved in this study will have extensive experience in mammographic interpretation, serving as the benchmark during the study. Details such as single or double screening readings and the utilisation of AI-assisted mammographic reading will be documented at each centre. Additionally, the integration of conventional mammogram studies with other radiological/histological findings will occur when deemed necessary by responsible investigators, who will record relevant variables in the electronic case report form (eCRF) following their usual clinical practice.

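### Detection by BI-RADS category compares mammography with its own score, and in mammogram-negative strata MammoWave's sensitivity is biased upward because its label triggers the ultrasound

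*Protocol article*

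**What the plan says.** All places are in the protocol article.

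- **Study outcomes** lists "BC detection rates of each system by BI-RADS classification" as a secondary outcome. A second outcome there also splits each system's detection by BI-RADS, together with histological type and size.
- **Hypothesis and objectives** has a related objective for MammoWave alone: "Evaluation of the sensitivity of MammoWave in detecting BC according to the American College of Radiology (ACR) BI-RADS classification". The same list treats detection rate and sensitivity as the same quantity.
- **Collected variables** includes "BI-RADS score of the screening mammographic study for each breast (2D or tomosynthesis) according to the degree of suspicion". This is the only BI-RADS score listed for every breast at screening.
- **Choice of comparator/control intervention** uses BI-RADS a second way, to code the reference standard. A result is positive "when BC presence is confirmed by histology (ie, BI-RADS 6), otherwise labelled as" negative (BI-RADS 1, 2 or 3). The section adds that "within this study BI-RADS 4 and BI-RADS 5 are only image suspicion criteria".
- **Study design** verifies the two phases differently. In phase 1 (500 women), "all asymptomatic volunteers will undergo conventional mammography and ultrasound (US) examinations at a minimum to ensure optimal diagnostic accuracy". In phase 2 (9500 women), if MammoWave's "AI label is positive, an US examination will be conducted (in addition to conventional mammography), particularly for women with dense breasts", unless it has already been done.
- **Follow-up** makes the 2-year follow-up of each volunteer the reference standard.

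**The concern.** Two separate faults meet in the BI-RADS-stratified outcomes.

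The first is circularity. The screening BI-RADS score is mammography's test result. Tabulating mammography's detection within levels of its own result returns the definition of a positive mammogram, not a finding about mammography.

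The second is verification that depends on the test under study. A cancer in a mammogram-negative breast (a category below the recall threshold) counts only once something brings it to histology. In phase 2 the written route at the index round is a positive MammoWave label. Cancers that MammoWave flags are therefore more likely to be found than those it misses, and its sensitivity in that stratum looks too high.

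This stratum matters. The Introduction motivates the device by mammography's weakness in dense breasts, where sensitivity may fall to 57.8%. Detection in mammogram-negative women is the result a reader would take as evidence that MammoWave finds what mammography misses.

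**Working it through.** **The plan's own figure.** The Buderer formula with sensitivity 0.75, a half-width of 10 points and prevalence 0.0092 gives 1.96² × 0.75 × 0.25 / 0.10² = 72.03 cancers, and 72.03 / 0.0092 = 7829 women. This agrees with the stated minimum of 8000. The point below does not depend on it, but it shows that the sample-size section uses 0.92% as total prevalence.

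**Mammography by its own score.** If recall follows the score, detection is 0% in every category below the threshold and 100% in every category above it. The article states no threshold, so the place of BI-RADS 3 is open. Each category is still all or none.

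**MammoWave in BI-RADS 4-5.** Work-up there follows the mammogram whatever the label, so sensitivity can be estimated.

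**MammoWave in mammogram-negative strata.** From the documents: 500 women have ultrasound whatever the label, and in 9500 it follows a positive label. Assumptions: true sensitivity s, the same in all strata; ultrasound finds a share u of the cancers it is applied to; a share f of the cancers still missed surfaces within 2 years, equal for flagged and unflagged; label-negative women in phase 2 have no other work-up; cancer rates are equal in the two phases.

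Let A = u + (1 − u)f, the share found where ultrasound is done. Then

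apparent sensitivity = 10 000sA / [10 000sA + (1 − s)(500A + 9500f)].

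At s = 0.75:

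| f | u = 0.5 | u = 0.8 | u = 1.0 |
|---|---|---|---|
| 0 (index round only) | 98.4% | 98.4% | 98.4% |
| 0.25 | 87.5% | 90.1% | 91.3% |
| 0.50 | 81.4% | 83.9% | 85.1% |
| 0.75 | 77.6% | 78.9% | 79.7% |
| 1 | 75.0% | 75.0% | 75.0% |

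The first row is 7500 / 7625. With s = 0.60 or 0.85 it becomes 96.8% or 99.1%, so a true difference of 25 points shows as 2.3 points.

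**Leaving out label-triggered cancers.** In phase 2 this gives s(1 − u) / [s(1 − u) + (1 − s)], since f cancels. At s = 0.75 it is 0.375 / 0.625 = 60% for u = 0.5 and 0.15 / 0.40 = 37.5% for u = 0.8. That is too low.

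**Number of cancers concerned.** Assume 40-50% of women have dense breasts and take the 57.8% from the Introduction. With 0.92% as total prevalence, 9500 × 0.4 × 0.0092 × 0.422 = 14.8 and 9500 × 0.5 × 0.0092 × 0.422 = 18.4 mammogram-negative cancers in dense breasts. With 0.92% as the mammogram-detected rate in dense breasts, the counts are 34.96 / 0.578 − 34.96 = 25.5 and 43.7 / 0.578 − 43.7 = 31.9. The range is about 15-32.

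**Timing.** Under Study period, recruitment runs from February 2024 to February 2026 and the first evaluation is due in December 2026. With uniform accrual (assumed), 10 / 24 = 42% of women have 2 years of follow-up by then, so results at that date would lie nearer the upper rows of the table.

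**The case against.** The strongest reply is that the plan already contains safeguards. All phase 1 women have ultrasound, and investigators may request other tests in either phase. The 2-year follow-up also counts cancers negative on both tests against the device. This stands, and it defeats a stronger reading: that MammoWave's rate in mammogram-negative women is bound to be 100%. That figure needs phase 2 alone with follow-up discarded, and the article plans no such analysis. The rate is biased, by an amount that depends on how many missed cancers surface.

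A reader might also infer from the reference coding that every cancer is BI-RADS 6, leaving a single cancer stratum. That is strained. The coding defines positive and negative for the reference standard, while the screening score is recorded separately and is the natural stratifier. The outcome simply does not name it.

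It can also be said that methods are left to the SAP, which is not shown, and that the MammoWave-only objective is untouched by the circularity. Both are fair. But the outcome as written extends to each system, and no analysis method makes mammography informative within its own score.

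Finally, the article has mammograms double-read before enrolment, which largely fixes the score before the label exists. Inclusion criterion 5, however, allows the mammogram on the same day as the MammoWave test or later.

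**Conclusion.** The concern holds in limited form. The between-system comparison by BI-RADS carries no information if recall follows the score; this follows from the definition and needs no numerical assumption. MammoWave's sensitivity in BI-RADS 4-5 is sound in this respect. In mammogram-negative strata it is biased upward. At an assumed true 75%, the bias is about 23 points on index-round cancers alone, about 6-10 points if half of the remaining cancers surface, and nil if all do. The size rests on assumed values of s, u and f and on equal surfacing of flagged and unflagged cancers. The direction holds whenever a larger share of flagged than of unflagged cancers is found in total. The documents do not support calling the MammoWave result predetermined. The outcomes are secondary, but following them as written would give one empty column and one flattering one.

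**What to change.** 1. State that the stratifier is the screening-mammogram BI-RADS score, recorded before the MammoWave label is seen.
2. Delete *of each system* from the BI-RADS-stratified outcomes and report MammoWave only, as the corresponding objective already does.
3. Report MammoWave's sensitivity in BI-RADS 4-5 as planned.
4. In mammogram-negative strata, report only after complete 2-year follow-up. Give the figure on all cancers as an upper bound beside the figure without label-triggered cancers as a lower bound, and present neither as an unbiased sensitivity. The lower figure must not stand alone, since it can read 37.5-60% when the truth is 75%.
5. Show label-triggered cancers separately, as extra cancers per 1000 women.

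This changes wording in the protocol and SAP and needs no new data. The cost is precision and time. Even if all of the 15-32 cancers in dense breasts surfaced, the 95% half-width at 75% would be 1.96 × √(0.1875 / 32) = 15 points to 1.96 × √(0.1875 / 15) = 22 points. The mammogram-negative results also could not be complete at the December 2026 evaluation.
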